### Data collection and follow-up

On the day of enrolment, pregnant women will be asked to complete an enrolment questionnaire providing information about general demographic characteristics and other factors influencing breastfeeding. Meanwhile, if the enrolment questionnaire finds prenatal depression among the participants, we will refer them to the department of psychology. Then, the ecological instantaneous evaluation of both groups will be performed every week to determine the trend of change in intention and emotions until delivery. The measurement of emotion uses the Positive and Negative Affect Scale (PANAS) and 10 positive items for positive emotions proposed by Fredrickson for validation.^24 25^ Postpartum questionnaires on breastfeeding behaviour during postnatal hospitalisation will be completed 1 week after delivery. Blood samples will be collected twice, after they are admitted to the hospital approaching delivery and after delivery at 7 to 8 am (vaginal delivery: the morning after one night; caesarean section: the morning after two nights), and evaluated for prolactin and IGF-I to evaluate postpartum lactation ability. The blood draw will be conducted by nurses in the ward.

On recruitment, general demographic variables will be collected: education, occupation, number of permanent household members, total average annual household income and expected date of birth. Other influencing factors will include mode of delivery, self-reported ease of breastfeeding, degree of sleep disturbance, self-reported importance of early exclusive breastfeeding, knowledge of breastfeeding, birth injury and nipple cracking pain scores, degree of hospital support, depression (measured by Edinburgh Postnatal Depression Scale, EPDS), anxiety (measured by Generalised Anxiety Disorder, GAD-7), breastfeeding intentions (measured by Infant Feeding Intentions Scale, IFI), breastfeeding behaviour score (LATCH), resilience (Brief Resilience Scale, BRS) and potential number of traumatic events.^26–31^ Generally, Baby-Friendly hospitals will take measures such as early sucking and skin-to-skin contact within 1 hour after delivery, limitation of bottle used, room-in, etc.^32^ We will also record and report routine measures taken in this Baby-Friendly hospital.

All questionnaires will be made through the questionnaire star website and distributed via WeChat. The corresponding data are stored in the questionnaire star account. Hormone test results will be recorded and saved manually. We will keep the personal information and data of each participant strictly confidential.

### Data analysis

Descriptive analyses will be performed to show the baseline characteristics of the participants. To assess the intervention effects over time, multivariate analysis of variance of repeated measuring will be taken for the change of positive and negative emotions, intention to breastfeed and resilience trend across the weeks. To test the association among positive/negative emotions, lactation-related hormones and breastfeeding behaviours, we will perform multiple linear regression or logistic regression in between and exploratory mediation analysis. To evaluate the effect of the intervention, we will take a two-sample t-test or Wilcoxon rank-sum test for quantitative data and a χ^2^ test for qualitative data.

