**Methods and analysis:**

This study is designed as a randomised controlled trial conducted in the Women’s Hospital School of Medicine at Zhejiang University and the Wuyi First People’s Hospital. The participants will be randomly divided into two groups using stratified random grouping: the intervention group will receive ‘Three Good Things’ intervention, while the control group will write about three things that come to mind first. These interventions will be continued from enrolment until the day of delivery. Maternal blood hormone levels will be tested approaching delivery and the following day after birth. Behavioural information about breastfeeding will be collected 1 week afterwards.

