### Recruitment

The study will be conducted in the Women’s Hospital School of Medicine at Zhejiang University. We will include primiparous pregnant women at 34–38 gestational weeks. The exclusion criteria are as follows:

Women with no intention to give birth in a designated hospital.Women not giving birth for the first time.Women with a disease that prevents breastfeeding (cardiac insufficiency, infectious diseases, neurological or cognitive damage, etc)Pregnant women with more than one fetus.

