### Sample size

Based on the results of the pilot study, statistical power (1−β) of 80%, and a two-tailed significance level (α) of 0.05, we calculated the targeted sample size with a two-sample t-test allowing unequal variance. Given the breastfeeding behaviour score (LATCH) was 12.72 in the intervention group (SD=2.33) and 12.06 in the control group (SD=1.51), the theoretical sample size was shown as N1=N2 = 141. Considering a dropout rate of 20%, the ultimate sample size needed was estimated at 353 individuals.

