### Intervention

At the fetal heart monitoring studio, we will ask the participants to add our Wechat account, and the subsequent communications and relevant questionnaire distribution will be carried out through Wechat chat software. In the T_1_ stage, participants will complete a series of intervention questionnaires. Participants in the intervention group will be asked to write down three good things that have happened during the day every 2 days, with weekly specific themes. Participants in the control group will only have to write about three things that come to mind first that are related to the same theme. To improve the compliance and interest of the participants, we will set up different instructions and themes for them weekly (table 1). Meanwhile, if a participant forgets to write, we will send out hints if they fail to complete the questionnaires. When the participant is unwilling to take the initiative to fill in the questionnaire, we will ask for reasons and send encouraging messages (eg, about the benefits of participating in the project). For ethical considerations of avoiding excessive disturbance, the participants will be regarded as loss-to-follow-up, after three non-responses.

**Table 1 T1:** Instructions for the intervention and control groups

Week	Topic	Instructions for the intervention group	Instructions for the control group
1	My baby	Please recall three good things that happened to you today related to you and your baby, and record them with the reasons why they happened. Here are some examples: My baby is moving today, and my baby is growing healthily. I saw a cute baby picture today, and my baby may be cuter. I bought baby’s little clothes today, they are so small and cute.	Please record the first three baby-related events that come to your mind today, and record them and the reasons why they happened. Here are some examples: I suddenly thought that it is not easy to have a child. I had the maternity check-up today.

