5	My life	Please recall three good things that happened to you today related to your life, and record them with the reasons why they happened. Here are some examples: Today, I listened to my favourite songs, which gave me a lot of inspiration and memories. Today, I found a gentle sentence on my phone, which said, ‘I was born mediocre, and I was born proud. Let’s be a happy ordinary person’. The emoticons my friend sent me today were so cute, I thought they were very interesting and funny.	Please record the first three life-related events that come to your mind today, and record them and the reasons why they happened. Here are some examples: I watch videos on the phone for an hour today. I watched a TV series with my husband this evening.

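### Repeated-measures MANOVA on weekly emotion and intention does not fit series whose length varies by design, so it must give up either later weeks or women

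*Protocol article*

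**What the plan says.** The Recruitment section sets the entry window: "We will include primiparous pregnant women at 34–38 gestational weeks". The abstract makes the length of exposure depend on delivery: "These interventions will be continued from enrolment until the day of delivery". Under Data collection and follow-up, "the ecological instantaneous evaluation of both groups will be performed every week to determine the trend of change in intention and emotions until delivery". Table 1 in the Intervention section lists five weekly themes. The same section adds a further source of incomplete series: "the participants will be regarded as loss-to-follow-up, after three non-responses".

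For these data, followed from week to week, the Data analysis section names one method: "multivariate analysis of variance of repeated measuring will be taken for the change of positive and negative emotions, intention to breastfeed and resilience trend". The section closes with a separate rule for comparing the arms: a two-sample t-test or Wilcoxon test for quantitative data and a chi-squared test for qualitative data.

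**The concern.** Standard repeated-measures MANOVA treats each woman's scores as one vector of fixed length and drops any woman with a gap in it. Here the length of the vector is set by gestation at entry and by date of delivery. A woman who enrols at 34 weeks and delivers at 40 has six full weeks; one who enrols at 38 weeks and delivers at 40 has two. No compliance effort can equalise them.

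Two things are at stake. One is information, since women or weeks have to be discarded. The other is whom the result describes. Complete series come mainly from early enrollers who deliver late, who are also the women with the longest exposure to the writing exercise. Delivery date is settled only after randomisation, so the analysed set is not defined by baseline characteristics alone.

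A smaller mismatch sits in the same sentence. It lists resilience among the weekly trends. The Study design section gives emotion and willingness as the weekly process variables, and Data collection and follow-up gives intention and emotions. The caption of Figure 1 does not name resilience in the baseline or intervention questionnaires. The Brief Resilience Scale appears only in the list of other influencing factors, with no weekly schedule.

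**Working it through.** **The plan's own figure.** The only sample-size figure is for the LATCH score. With SDs 2.33 and 1.51 and a difference of 12.72 − 12.06 = 0.66, the normal approximation is n = (2.33² + 1.51²)(1.960 + 0.842)² / 0.66² ≈ 138.9 per arm. The unequal-variance t-test first reaches 80% power at 141 (0.8027, against 0.7999 at 140). Then 2 × 141 / 0.8 = 352.5, rounded up to 353. The stated figures reproduce. They have no bearing on the weekly analysis beyond supplying 353 as a denominator.

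**What follows from the text alone.** Completed weeks = whole weeks between enrolment and delivery. Five completed weeks require delivery at or after:
- 34 + 5 = 39 weeks for entry at 34
- 36 + 5 = 41 weeks for entry at 36
- 38 + 5 = 43 weeks for entry at 38

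**A check by hand.** Suppose entry is uniform over 34–38 weeks and every woman delivers at week D. The share with at least k completed weeks is (D − k − 34)/4, limited to between 0 and 1. At D = 40 this gives 100% for k = 2, 75% for k = 3, 50% for k = 4 and 25% for k = 5. At D = 39 it gives 75%, 50%, 25% and 0%.

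**With spread in delivery.** The article gives no distribution of entry or delivery, so everything below is assumed. In the main case, entry is uniform over 34–38 weeks. Delivery is normal with mean 39.0 (SD 1.3), 39.3 (SD 1.2) or 39.6 (SD 1.2) weeks, after enrolment and no later than 41.5 weeks. The wider case uses means of 39.0–40.0, SD 1.2, with delivery after enrolment and no later than 42 weeks. The last two columns vary the wider case.

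| Completed weeks | Occasions with baseline | Main case | Wider case | Wider case, independent 20% dropout | Wider case, entry up to 39 weeks |
|---|---|---|---|---|---|
| 2 | 3 | 74–84% | 73–88% | 58–70% | 61–77% |
| 3 | 4 | 52–64% | 50–71% | 40–56% | 41–58% |
| 4 | 5 | 30–41% | 28–48% | 23–38% | 22–38% |
| 5 | 6 | 13–20% | 12–25% | 9–20% | 9–20% |

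The second column matters because emotion and intention are also measured at baseline, so k completed weeks give k + 1 occasions. Of 353 women, the main case leaves about 46 to 71 with five completed weeks (353 × 0.13 and 353 × 0.20), and about 184 to 226 with three (353 × 0.52 and 353 × 0.64).

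**Sensitivity to entry.** If every woman enrolled at exactly 34 weeks, 50–79% would complete five weeks under the wider-case delivery assumptions. If every woman enrolled at 38 weeks, none could complete four before 42 weeks.

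**The case against.** The strongest reply is that the article never says how many weeks enter the model, how series are aligned, or that incomplete cases are deleted. Five is inferred from the writing themes in Table 1, which schedule topics rather than analysis time points. Such details are commonly left to an analysis plan, and this is a condensed article. That stands, and their absence is not criticised here. What remains is the choice of method, which the article does state and which an analysis plan following it would inherit.

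A reader might infer that most women will be deleted. The documents do not support that without conditions. It follows under the assumptions above if four or five completed weeks are analysed. It is borderline at three and fails at two, and it may also fail for five weeks if nearly all women enrol at 34 weeks.

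A reader might also infer that the effect of the intervention on emotion, the first step in Hypotheses 1a and 1b, can be tested only through this MANOVA. That does not hold either. Postpartum emotion and postpartum breastfeeding intention are secondary outcomes under Evaluation and outcomes, and the closing rule of the Data analysis section compares them between arms without any weekly series. The association and mediation analyses are separate regressions.

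Finally, the exact form of a replacement model is partly preference. Several specifications would serve.

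**Conclusion.** The point holds as a mismatch between the stated method and the stated measurement schedule. That series differ in length follows from the text and needs no assumption. How many women would be lost does depend on assumptions: entry spread evenly over 34–38 weeks, delivery as specified above, and deletion of incomplete cases as in standard MANOVA. On those terms the plan must choose. The full five-theme programme would be analysed in roughly one woman in eight to one in five, selected for early entry and late delivery. Alternatively, most women are kept and only the first two or three weeks are used.

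The damage is confined to the weekly trajectory of emotion and intention, which the article treats as process variables. The primary outcomes, the sample size and the two-group comparison of postpartum emotion and intention are untouched. The change should be made, but the trial's main conclusions do not turn on it. The resilience mismatch is minor and needs no assumption: as described, there is no weekly resilience series to analyse.

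**What to change.** Replace the repeated-measures MANOVA with a linear mixed model on all available weekly scores. Use fixed effects for arm, week since enrolment, arm-by-week, baseline score and the randomisation stratum (level of family support), and model the within-woman correlation. Report the arm difference at one prespecified week with good coverage. Under the assumptions above, week 2 would be reached by about three quarters or more of women before allowing for non-response.

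For resilience, either remove it from the weekly trend or state that its scale is part of the weekly questionnaire.

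For emotion and intention the cost is analysis wording only, with no new data. The small downside is that the model assumes a form for the time trend and the correlation, and treats weekly scores that would fall after delivery as not observed. Reporting at an early, well-covered week limits how much rests on that. Keeping resilience as a weekly outcome would cost extra questionnaire items if the scale is not already collected weekly.

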### Data monitoring

The data monitoring committee is composed of members of the Science and Education Department of the hospital. As the administrative department of the hospital, the Ministry of Science and Education is in charge of scientific research and reviews the integrity of scientific research to ensure the authenticity of data.

### Patient and public involvement

The development of the research question and outcome measures is not influenced by patients’ priorities, experiences and preferences. Participants and the public do not involve in the design, recruitment or conduct of the study. We will disseminate the results to study participants through subsequent publications. For this RCT, the burden of the intervention is assessed by the patients themselves through the questionnaire.

## Discussion

Our study has several strengths. First, as distinct from current interventions focusing on knowledge improvement, our study attempts to promote the secretion of lactation-related hormones by elevating positive emotions, then breastfeeding behaviours. Second, most previous interventions promoting breastfeeding were set in the postpartum period. Considering the importance of early breastfeeding experiences, we moved the intervention period to the late stages of pregnancy. Third, earlier mixed educational and supportive interventions are difficult to evaluate and replicate precisely. Our study will use the typical psychological measures, ‘Three Good Things’, to boost positive emotions, which is feasible for individuals to carry out and can be easier to promote and popularise among pregnant women.

This study also has several limitations. First, due to the restrictions of the testing technology and the intricacies involved in distinguishing between endogenous and exogenous sources, we will not test for oxytocin in the serum, although this has been widely reported to be associated with lactation. However, oxytocin release is related to prolactin levels, which will be included in our test.^33^ Second, we limit the outcome measurement of breastfeeding-related behaviours to the postpartum hospitalisation period, without following a 6 month or longer period. Nevertheless, exclusive breastfeeding in the early postpartum period (1 hour and within a few days after delivery) has been positively correlated with the duration of breastfeeding after delivery.

In conclusion, this study will test the effect of ‘Three Good Things’ intervention both on the emotions of women during pregnancy, and also on the secretion of colostrum and breastfeeding behaviours as well. This study will also help us to further identify the physiological mechanisms of the association between emotions and breastfeeding behaviours.

## Ethics

This study involves human participants. The study has been approved by the Ethics Committees of the Women’s Hospital School of Medicine at Zhejiang University (20190088) and the Wuyi First People’s Hospital (20210001). Participants gave informed consent to participate in the study before taking part.
